### Intervention Description

This study involves 3 groups, each with specific treatment protocols, shown in Table 1. All 60 eligible participants will be thoroughly informed about the study protocol, and their consent will be obtained. They will be randomly divided into 3 groups: group A, group B, and group C. In group A, participants will receive honey thermal microcautery 2 times (first and seventh days) and placebo capsules for 7 days. Group B will receive standard physiotherapy once a day along with placebo capsules for 7 days. Group C will receive *S cordifolia* oil via 8 drops in each nostril and placebo capsules for 7 days. All baseline parameters will be recorded at the beginning of the trial. This study conforms to the SPIRIT guidelines, ensuring standard execution and ethical handling of the clinical trial. Placebo capsules will be identical in appearance, taste, and administration schedule to mimic a real medication. These will be administered alongside the active intervention twice daily after food, ensuring blinding and consistency throughout the study.

**Table 1. T1:** Grouping and posology.

Group	Intervention	Dose and frequency	Procedure time (min)	Duration (d)	Follow-up
A	Honey thermal microcautery+placebo	2 times a wk	20-30	2 (first and seventh)	On the 8th, 16th, and 32nd days
B	Standard physiotherapy+placebo	Once a day (in the morning)	30-60	7	On the 8th, 16th, and 32nd days
C	*Sida cordifolia* oil via nasal route+placebo	8 drops once a day	20-30	7	On the 8th, 16th, and 32nd days

Study drugs will be stored in a secure location and administered to the participants only under the direction of the investigator. Drug dispensing records will be kept. Any imbalance in the quantities dispensed and returned will be explained.

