#### Primary Variable: Abduction Improvement

The primary variable, shoulder abduction improvement, was used to calculate the minimum sample size required for the study, ensuring adequate power to detect a meaningful difference between groups. The primary variable in this study is shoulder abduction improvement, measured as the increase in the range of motion after the intervention. Based on expected differences, variability, significance level, and power, the minimum sample size required was calculated to ensure reliable detection of a meaningful improvement

Where the mean score for abduction in *shudhabala taila nasya* pre=2.23 (as per the study by Revathi et al [22]).

Mom score for abduction in *shudhabala taila nasya* post at follow-up=1.06.

Difference (pretest-posttest)=1.17

SD=0.58.

Considering 45% superiority in the thermal microcautery group=(1.17) × 45 = 0.526

Mean differenсе *δ*=0.526

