#### Minimum Sample Size Required

Based on expected differences, variability, significance level, and power, the minimum sample size required was calculated to ensure reliable detection of a meaningful improvement:

n=1=2=2 × (1.96 + 0.84)^2^ × (0.58)^2^/(0.526)^2^=20 per group

Total samples = 20 × 3 per group=60

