### Statistical Methods

One-way ANOVA will be applied to compare the means of the 3 groups. If ANOVA indicates a significant difference, post hoc tests will be further applied (eg, the Tukey honestly significant difference test) to identify which group differs. A *P* value of <.05 will be considered statistically significant. Covariates such as age and baseline severity will be considered, and adjustments will be made using analysis of covariance if needed. The analysis will be intention to treat, with missing data handled through multiple imputation. Statistical assistance will be provided by a statistician or someone skilled in statistics. We will use SPSS (version 26; IBM Corp) for statistical analysis.

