## Discussion

### Anticipated Findings

A group of 20 participants will receive honey thermal microcautery, another group of 20 participants will receive standard physiotherapy, and another group of 20 participants will receive *S cordifolia* oil through the nasal route. All 3 groups will receive the treatment for 7 days. On the 8th, 16th, and 32nd days, we will assess the patients using the VAS, the SPADI, the McGill Pain Questionnaire, and ROM. We will compare the changes before and after therapy. We expect that the interventional group, specifically the honey thermal microcautery group, will exhibit statistically significant outcomes.

The study evaluated the efficacy of *mahamasha taila brihana nasya*, administered as 8 drops in each nostril per session, over 2 sessions spaced 7 days apart, along with 3 sittings of *agni karma* performed once weekly on the same day. In contrast, the third group (group C), both *mahamasha tailabrihana nasya* and *agnikarma* were administered. The assessments were taken on days 0, 7, 14, 21, and 28 using the VAS, the SPADI, the McGill Pain Questionnaire, and ROM goniometric examination. Improvement was observed in all 3 groups, especially the group in which both treatment modalities were administered.

A systematic review [32] compiled different studies on FS and thermal microcautery.

Van’t Hoff’s principle states that, for every degree that the body temperature rises, the body’s basal metabolism increases by a specific proportion. An increase in temperature causes muscles to relax, which reduces discomfort and inflammation associated with muscle spasms. This can be achieved via thermal microcautery [33]. Similar to infrared fomentation, the light waves cause inflammation to be reduced by penetrating deeper into the body; thermal microcautery similarly causes the local capillaries to dilate, improving the blood supply to the affected area and eliminating inflammatory compounds [34].

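### The group comparison is an unadjusted one-way ANOVA with no stated response, and ANCOVA is left to an undefined condition; one ANCOVA on baseline, fixed in advance, would gain precision and close the choice

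*Protocol article*

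**What the plan says.** The Statistical Methods section names the main comparison: "One-way ANOVA will be applied to compare the means of the 3 groups". Tukey comparisons follow if that test is significant, and "A *P* value of <.05 will be considered statistically significant". Adjustment comes next, as a possibility only: "Covariates such as age and baseline severity will be considered, and adjustments will be made using analysis of covariance if needed". The section gives no criterion for need, introduces the covariates as examples, and does not say whether the adjusted or the unadjusted result decides.

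It also does not state the response variable. Two other places point to a change from baseline. Under Primary Variable: Abduction Improvement: "The primary variable in this study is shoulder abduction improvement, measured as the increase in the range of motion after the intervention". Under Anticipated Findings: "We will compare the changes before and after therapy".

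The data for adjustment will exist. Intervention Description states: "All baseline parameters will be recorded at the beginning of the trial".

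**The concern.** There are two separate issues.

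**Precision.** The trial has 20 patients per arm and admits both the inflammatory and the frozen stage, so patients will differ at entry. The baseline of the same measure usually explains part of the follow-up value. A change score uses it by subtraction, which is generally not the most efficient way. An unadjusted comparison of final values does not use it.

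**Choice of model.** Because the condition for ANCOVA is undefined, both fits can be produced and the decision taken afterwards. If the more favourable P value decides, the nominal 5% level no longer holds. The Results section says that data analysis is already in progress, and the Discussion names the arm expected to do best. These are circumstances in which the model should be fixed beforehand.

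**Working it through.** **Inputs from the protocol article**
- Difference: "Considering 45% superiority in the thermal microcautery group=(1.17) × 45 = 0.526". The factor 45 must be read as 0.45: 1.17 × 0.45 = 0.5265, used as 0.526.
- SD = 0.58, not labelled as the SD of a final score or of a change.
- Three arms of 20, 1:1:1.

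**Assumptions**
- The correlation r between baseline and follow-up is not given; 0.3, 0.5 and 0.7 are used.
- The SD is equal at baseline and follow-up.

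**1. The plan's own figure.** "n=1=2=2 × (1.96 + 0.84)^2^ × (0.58)^2^/(0.526)^2^=20 per group". The formula gives 2 × 2.80² × 0.58² / 0.526² = 19.06, which rounds up to 20. The figure reproduces, with 81.8% power by the normal approximation. It is a two-group calculation without adjustment.

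**2. Relative variance.** With common SD σ:
- final-value ANOVA: σ²
- change-score ANOVA: 2σ²(1 − r)
- ANCOVA: σ²(1 − r²)

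So ANCOVA/final = 1 − r² and ANCOVA/change = (1 + r)/2.

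| r | ANCOVA / final | ANCOVA / change |
|---|---|---|
| 0.3 | 0.91 | 0.65 |
| 0.5 | 0.75 | 0.75 |
| 0.7 | 0.51 | 0.85 |

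The reduction is 9–49% against final values and 35–15% against change scores. ANCOVA is the more precise analysis in every cell.

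**3. Power of one Tukey comparison at 20 per arm.** The standardised difference is d = 0.526/0.58 = 0.907 and the noncentrality is d × √(20/2) = 2.868. The Tukey critical value for three groups on 57 degrees of freedom is 2.406 on the t scale, which gives 68% unadjusted. (This sets aside the requirement that the overall F test be significant first.) Under ANCOVA, d is divided by √(1 − r²) if 0.58 is a final-score SD, or by √((1 + r)/2) if it is a change SD.

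| r | d, final-score SD | Power | d, change SD | Power |
|---|---|---|---|---|
| 0.3 | 0.951 | 72% | 1.125 | 87% |
| 0.5 | 1.047 | 81% | 1.047 | 81% |
| 0.7 | 1.270 | 94% | 0.984 | 76% |

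The gain runs in opposite directions with r under the two readings, so the 94% and the 87% must not be quoted without stating which SD is meant.

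**4. Type I error of choosing the model afterwards.** Simulation under no treatment effect, 3 × 20 patients, 10,000 runs per r.

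| Rule | r = 0.3 | r = 0.5 | r = 0.7 |
|---|---|---|---|
| Final-value ANOVA alone | 5.3% | 5.0% | 5.2% |
| ANCOVA alone | 5.3% | 5.3% | 5.4% |
| Smaller P of final-value ANOVA and ANCOVA | 6.8% | 7.7% | 8.7% |
| Smaller P of change ANOVA and ANCOVA | 8.3% | 8.1% | 7.6% |
| Smallest P of four models (final ANOVA, change ANOVA, ANCOVA on baseline, ANCOVA on baseline and age) | 10.2% | 10.7% | 11.2% |
| ANCOVA only if a baseline test gives P < 0.05, otherwise final-value ANOVA | 5.2% | 4.6% | 3.8% |

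Inflation appears when results decide the model, and not when baseline imbalance alone does.

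**The case against.** **Is baseline thrown away?** A reader might infer this from the Statistical Methods section read alone. The documents do not support it. The primary variable is described as an increase, the Discussion speaks of comparing changes, and baseline severity is named as a candidate covariate. What stands is that the section leaves the response unstated, and that neither possible response uses baseline as well as ANCOVA does.

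**Is the ANOVA invalid?** No. Under 1:1:1 randomisation, ANOVA of final values or of changes is unbiased and keeps its level. Chance imbalance is already reflected in its standard error. The cost is precision.

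**Does any data-dependent adjustment inflate error?** No. A trigger based on baseline imbalance alone did not inflate it in the simulation, and the protocol does not propose choosing by P value. What stands is that its wording does not exclude that route.

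**Would a statistical analysis plan settle this?** The exact covariate list is detail that an article may leave to a fuller document. But the article does more than omit detail: it states the less efficient model as the main test and makes the better one discretionary.

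**Do the gains rest on unknowns?** Yes. The documents give neither r nor the type of SD. The size of the gain is uncertain; its direction is the same across the range shown.

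**Conclusion.** The point holds as a weakness of efficiency and pre-specification, not as an error that invalidates the analysis. The Statistical Methods section makes an unadjusted ANOVA the group comparison, does not name its response, and leaves ANCOVA to an undefined condition.

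For r between 0.3 and 0.7, moving to ANCOVA cuts variance by 9–49% relative to final values or by 35–15% relative to changes. Power for one Tukey pair rises from 68% to between 72% and 94%, depending on r and on what the SD of 0.58 measures. The inflation to about 7–9%, or about 10–11% with four candidate models, is what the wording permits if P values decide; it is not a forecast of what the investigators will do.

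A reader might also infer that the sample size is wrong. This point does not show that: 20 per group reproduces from the stated formula and needs no change on this ground.

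**What to change.** Replace the ANOVA sentence and the conditional adjustment sentence in Statistical Methods, and align the Abstract, with wording such as:

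*Each continuous outcome at each stated visit (days 8, 16 and 32) will be analysed by ANCOVA of the follow-up value, with treatment group and the baseline value of the same measure as terms, whatever the observed baseline balance. The overall group test and the multiplicity-adjusted pairwise contrasts will be taken from this model. Unadjusted one-way ANOVA will be reported as a sensitivity analysis only.*

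If age is wanted as a covariate, name it now; otherwise leave it out. Name the pairwise adjustment as well. State under Primary Variable: Abduction Improvement whether 0.58 is the SD of a final score or of a change, so that the expected gain can be quoted correctly.

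This fixes the model. It does not choose between visits or outcomes, which is a separate matter.

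The cost is a dated wording change. It needs no additional patients, measurements or software. Because analysis is reported as in progress, the change should be made before outcomes are compared between arms any further, and the amendment should say what had been seen by then.

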### Ethical Considerations

All study interventions and treatments will be provided completely free of cost, and participants will not be charged for any procedures, assessments, or related expenses.

#### Overview

Ethics approval from the Institutional Ethics Committee of Mahatma Gandhi Ayurved College Hospital and Research Centre was received (MGACHRC/1EC/Sep-2023/74) on September 18, 2023. The Clinical Trials Registry India registration number for this study is CTRI/2023/11/059594. The committee will oversee the trial’s advancement and determine its conclusion. The researcher shall evaluate any unfavorable event and report it to the ethics committee. The participants will be provided with written research details in 2 languages (Marathi and English), and written consent will be obtained from the participants on an informed consent form. They will be informed about the confidentiality of their details. Safety will be monitored by recording any adverse events during the entire study. We will make sure that no photos include any identifiable participants.

#### Consent

The patients will be fully informed about the study’s purpose and provide signed consent before the study commences. The researcher will personally ensure that participants understand the information and voluntarily agree to participate in the trial.

Private information about the participants will be collected and kept confidential before, during, and after the trial. The consent form will include specific information about the study purpose, procedures, potential risks and benefits, confidentiality measures, and the voluntary nature of participation. Participant comprehension will be assessed through a follow-up discussion, allowing them to ask questions and clarify their understanding.

#### AR Management

In the event of ARs during the trial, the affected participants will receive treatment at the institute’s attached hospital. The investigator will cover the costs associated with the treatment to ensure the participants’ safety.

#### Intervention Modification

Any negative effects noted during the treatment will be recorded and immediately reported to the ethics committee. The patients will receive the necessary treatment for the negative effects. If participants opt out of the treatment, they will be asked why, and this will be carefully documented.

### Previous and Concomitant Medication

Patients will be allowed to continue their allopathic medications for diabetes mellitus and hypertension, anticoagulant therapy, or hormonal medications as per their existing treatment regimen. Any analgesics will be discontinued during the study period to prevent bias or interference with the study outcome. The investigator will record any medication taken by the patients other than the protocol drugs via any route.

## Results

Preliminary data collection is ongoing, and participant recruitment for the study commenced in October 2024. As of January 2025, a total of 16 participants have been recruited across all 3 study groups. Data analysis is currently in progress. The final results of the study are expected to be published in November 2025. The study’s findings will be disseminated through peer-reviewed publications.

## Discussion

### Anticipated Findings

A group of 20 participants will receive honey thermal microcautery, another group of 20 participants will receive standard physiotherapy, and another group of 20 participants will receive *S cordifolia* oil through the nasal route. All 3 groups will receive the treatment for 7 days. On the 8th, 16th, and 32nd days, we will assess the patients using the VAS, the SPADI, the McGill Pain Questionnaire, and ROM. We will compare the changes before and after therapy. We expect that the interventional group, specifically the honey thermal microcautery group, will exhibit statistically significant outcomes.

The study evaluated the efficacy of *mahamasha taila brihana nasya*, administered as 8 drops in each nostril per session, over 2 sessions spaced 7 days apart, along with 3 sittings of *agni karma* performed once weekly on the same day. In contrast, the third group (group C), both *mahamasha tailabrihana nasya* and *agnikarma* were administered. The assessments were taken on days 0, 7, 14, 21, and 28 using the VAS, the SPADI, the McGill Pain Questionnaire, and ROM goniometric examination. Improvement was observed in all 3 groups, especially the group in which both treatment modalities were administered.

A systematic review [32] compiled different studies on FS and thermal microcautery.

Van’t Hoff’s principle states that, for every degree that the body temperature rises, the body’s basal metabolism increases by a specific proportion. An increase in temperature causes muscles to relax, which reduces discomfort and inflammation associated with muscle spasms. This can be achieved via thermal microcautery [33]. Similar to infrared fomentation, the light waves cause inflammation to be reduced by penetrating deeper into the body; thermal microcautery similarly causes the local capillaries to dilate, improving the blood supply to the affected area and eliminating inflammatory compounds [34].

Physiotherapy, such as wheel and step ladder exercises, aids in FS by enhancing joint mobility and flexibility. Wheel exercise allows for gradual stretching, whereas step ladder exercise improves shoulder strength and ROM. Together, they facilitate functional recovery and improve ROM. Our hypothesis is that honey thermal microcautery will yield more effective results than standard physiotherapy and *S cordifolia* oil via the nasal route because of its instant and satisfactory benefits. This research may guide future studies, incorporating traditional and modern methods, thus providing a well-rounded treatment for FS. This study seeks to guide clinical decisions by systematically comparing these interventions, enabling the choice of a more effective and individualized treatment for FS. This study compares diverse interventions, uses multidimensional assessment tools, and integrates Ayurvedic principles with modern therapy. It provides a new perspective into honey thermal microcautery; thus, clinicians can fine-tune effective treatments for FS. The limitation of this study is the small sample size, which, while adequate for preliminary insights, may limit the generalizability of the findings. Future studies with larger cohorts and extended follow-up periods are recommended to validate and enhance the applicability of the results. The primary findings will establish that honey thermal microcautery, standard physiotherapy, and *S cordifolia* oil via nasal administration effectively manage FS, ultimately determining which provides the best outcome.

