### Rationale of the Study

The 3 arms in our study were selected considering their unique mechanisms of action to adequately treat FS. Honey thermal microcautery is an Ayurvedic treatment with thermal effects. Standard physiotherapy is the classic gold standard, ensuring a robust comparator. *Sida cordifolia* oil via nasal route was selected considering its efficacy for *vata-kapha* disorders, particularly musculoskeletal diseases. These treatments were selected considering the evaluation and comparison of diverse approaches between modern medicine and traditional medicine toward optimal outcomes.

No study has been published comparing honey thermal microcautery, standard physiotherapy, and *S cordifolia* oil nasal administration. Additionally, no study has explored the use of honey thermal microcautery in FS. Considering these gaps, this study is essential to determine the most effective and safe therapeutic approach for FS, evaluating interventions such as honey thermal microcautery, standard physiotherapy, and *S cordifolia* oil nasal administration to identify treatments that optimize recovery time and minimize associated concerns.

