## Methods

### Overview

This study is an interventional, randomized, single-blind (assessor), 3–parallel arm study to compare the efficacy of honey thermal microcautery versus standard physiotherapy versus *S cordifolia* oil via nasal administration in the management of FS. We will intervene using honey thermal microcautery 2 times (the first and seventh day) along with placebo capsules twice daily for 7 days. Standard physiotherapy will be administered once a day along with placebo capsules twice daily for 7 days. *S cordifolia* oil via nasal administration will be administered via 8 drops in each nostril along with placebo capsules twice daily for 7 days. Follow-up will be conducted on the 8th, 16th, and 32nd days. Placebo capsules will be administered to reduce the psychological effect that patients might feel from knowing that they are not receiving any oral medicine, especially in the honey thermal microcautery group, where the treatment is administered only 2 times a week.

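### The article says the trial will establish that all three treatments work, but a trial with only active arms and a between-arm test can show only which arm does better

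*Protocol article*

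**What the plan says.** Near the end of Anticipated Findings the article states: "The primary findings will establish that honey thermal microcautery, standard physiotherapy, and" the nasal oil are effective in frozen shoulder. It then adds, as a further result, that the trial will determine which is best. The Conclusions section describes the expectations as preliminary theories, yet says that final conclusions on how efficacious each treatment is will follow the analysis. The Objective in the Abstract likewise names evaluating efficacy as a primary aim alongside comparing the arms.

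On the design:

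- Each arm has its own active intervention. For group A, Intervention Description says: "In group A, participants will receive honey thermal microcautery 2 times (first and seventh days) and placebo capsules for 7 days". Groups B and C receive physiotherapy and nasal oil respectively, with the same capsules.
- The capsule's purpose is given in the Methods Overview: "Placebo capsules will be administered to reduce the psychological effect that patients might feel". Intervention Description adds: "Placebo capsules will be identical in appearance, taste, and administration schedule to mimic a real medication".
- The hypothesis is one of superiority: "Our hypothesis is that honey thermal microcautery will yield more effective results than standard physiotherapy" and than the nasal oil.
- The analysis in Statistical Methods is: "One-way ANOVA will be applied to compare the means of the 3 groups", followed by Tukey comparisons if it is significant.
- Baseline enters in two places. The Secondary Objective defines sustained relief as at least 50% improvement on baseline, and Anticipated Findings says: "We will compare the changes before and after therapy".

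**The concern.** Whether a treatment works and whether it works better than another treatment are different questions. The first needs a reference that shows what happens without the treatment. This trial has none. The capsules are placebo in name but not a placebo control, because every arm takes them; they add the same expectation to every arm.

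Two routes to a claim that all three treatments work are then left, and neither is sound. One is improvement from baseline within each arm, which combines any treatment effect with natural course, regression to the mean in patients recruited while symptomatic, and expectation (only the assessor is blind). The other is a between-arm comparison, which does not address the question. The article says its results should guide clinical decisions, so an efficacy statement of this kind would be taken at face value.

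**Working it through.** **1. What the sample size supports.** Inputs from the Sample Size section: SD 0.58; difference between arms 0.45 × 1.17 = 0.526; Z values 1.96 and 0.84.

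n per arm = 2 × (1.96 + 0.84)² × 0.58² / 0.526² = 19.06, rounded up to 20, which gives 60 in all.

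The stated figure reproduces. It sizes one pairwise superiority comparison (power about 0.82 at 20 per arm). It does not size any test of whether an arm works.

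**2. What the planned test can see.** Write the expected improvement in arm k as c + τₖ. Here c is the improvement that would occur without any specific treatment effect, and τₖ is the specific effect of treatment k.

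- Between arms: (c + τ_A) − (c + τ_B) = τ_A − τ_B. The common part c cancels.
- Within an arm: c + τₖ. The two parts cannot be separated.

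Now take two opposite truths, using the improvement of 1.17 in the Sample Size section as an illustration for all arms:

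| Truth | c | τ in A, B, C | Expected improvement per arm | Expected differences |
|---|---|---|---|---|
| No treatment works | 1.17 | 0, 0, 0 | 1.17 | 0 |
| All treatments work | 0 | 1.17, 1.17, 1.17 | 1.17 | 0 |

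With equal spread, the data have the same distribution in both rows. The ANOVA at the 5% level is non-significant in about 95% of trials under either (simulation of 100,000 trials: 0.950). Nothing in this design tells the rows apart.

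**3. What a non-significant ANOVA means.** Suppose one arm is truly better by d and the other two are equal, with 20 per arm and SD 0.58 (assumed to be the SD of the analysed quantity in every arm). The noncentrality is 20 × (2/3) × d² / 0.58², on 2 and 57 degrees of freedom.

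| d | Noncentrality | ANOVA power | Non-significant |
|---|---|---|---|
| 0.526 | 10.97 | 0.83 | about 17% |
| 0.4 | 6.34 | 0.59 | about 41% |
| 0.3 | 3.57 | 0.36 | about 64% |

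The Tukey 95% half-width for a pairwise difference is about 0.44, which is 84% of the planned difference (0.44 / 0.526). A non-significant result therefore leaves room for differences close to the size the trial was built to find.

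**4. What a significant ANOVA means.** It ranks arms. If physiotherapy is accepted from outside evidence as effective, an arm that beats it gains support. Physiotherapy's own effect is then a premise and not a finding, and the effect of the lowest-ranked arm stays undetermined. No pattern of between-arm results establishes all three.

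**The case against.** Four objections deserve weight.

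*The sentence is an expectation, and it is hedged.* It stands under Anticipated Findings in the Discussion, not in an objective or an analysis rule, and the Conclusions leave the final word to the data. This stands in part: it would be wrong to say that the conclusion is fixed whatever the truth. But the hedge still promises a conclusion on the efficacy of each treatment, which is the part the design cannot supply.

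*The design suits its main question.* A randomized comparison of active arms is a legitimate way to ask which treatment is best, and most of the stated aims are comparative. This stands. The fault is in the claim, not in the choice of arms.

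*No before-after test is planned.* Statistical Methods lists none, and the sentence on changes before and after therapy can be read as change scores compared between arms. The Secondary Objective also speaks of comparing groups. This stands too. A reader might be tempted to show how easily a paired test would reach significance, but that would apply figures from a nasal-oil study, under an assumed SD of change, to a test the article does not plan.

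*Nothing says that a non-significant ANOVA will be taken as proof that all arms work.* Correct. Statistical Methods says only what follows a significant result. A reader might infer the misreading, but the text does not support it as a prediction.

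A reader might also go further and attack the comparator, since the Rationale says: "Standard physiotherapy is the classic gold standard, ensuring a robust comparator". That is a separate matter. The Introduction sets no content or duration for standard physiotherapy, so the documents do not show that group B falls short of it.

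**Conclusion.** The point holds in limited form. The article announces a result, efficacy of all three treatments, that its design and planned test cannot produce. What they can produce is a comparison between arms.

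The overclaim itself has no numerical size: the documents give no rate of improvement without treatment over 32 days, so the share of any improvement that is not due to treatment is unknown. The cancellation of the common improvement is algebra and needs no figures. The rates for a non-significant ANOVA rest on the article's SD of 0.58 applying equally in all arms.

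The sample size, the test and the data collection are not affected. Because the error concerns what may be concluded, it should be corrected before results are reported.

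**What to change.** Replace the sentence in Anticipated Findings with wording such as:

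> Conclusions will be limited to differences between the three arms, reported with confidence intervals. Change from baseline within an arm will be described and will not be taken as evidence of efficacy. A non-significant ANOVA will not be taken to show that the arms are equivalent or that all are effective.

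Align the Objective in the Abstract and the Conclusions section with this, so that they speak of comparing the treatments and not of establishing the efficacy of each. In the limitations, which now give the small sample size, add that there is no untreated or sham-treated control.

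The cost is a narrower claim. Nothing changes for patients, visits, sample size, data or the planned ANOVA.
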